## Abstract

**Introduction:**

Harmonica playing mimics pursed-lip breathing and strengthens respiratory muscles. Combined with music therapy, it may improve both pulmonary and mental health in chronic obstructive pulmonary disease (COPD) patients, though its effects are not well understood. This protocol outlines a randomized controlled trial (RCT) to evaluate the effectiveness of integrating harmonica playing into pulmonary rehabilitation (PR) programs.

**Methods and analysis:**

This single-center, two-arm RCT will be conducted at a tertiary hospital in Guangzhou, China. A total of 248 adult patients (with a clinical diagnosis of COPD but without severe comorbidities, significant cognitive impairments, and prior experience with the intervention components) will be randomized in a 1:1 ratio to either a harmonica-integrated PR group (intervention) or a standard PR group (control) for 6 months of home-based, tele-supervised training. The intervention will incorporate harmonica sessions in addition to standard PR exercises (breathing and physical exercises). Both groups will undergo in-hospital training sessions, supplemented by daily home practice under remote supervision by PR staff. The primary outcome is lung function (measured by FEV_1_%), while secondary outcomes include respiratory muscle strength, exercise capacity, fatigue, dyspnea, symptom burden, mental health, self-efficacy, quality of life, social support, adherence, and patient satisfaction. Statistical analyses will employ mixed-effects models with an intention-to-treat approach.

**Conclusion:**

This trial will evaluate the efficacy of a harmonica-integrated, home-based PR program with tele-supervision for COPD patients on lung function, respiratory muscle strength, exercise capacity, and overall health. If effective, it could offer a novel, affordable, and accessible home-based PR approach for COPD management.

**Trial registration number:**

ClinicalTrials.gov: NCT05995847.

## 1 Introduction

Chronic obstructive pulmonary disease (COPD), the third leading cause of death globally, is characterized by dyspnea, cough, and sputum production, often accompanied by peripheral muscle dysfunction, cardiovascular disease, anxiety, depression, and chronic fatigue (1, 2). Pulmonary rehabilitation (PR), a cornerstone of non-pharmacological COPD treatment, typically integrates self-management education, respiratory training, psychosocial support, and structured exercise, effectively improving lung function, alleviating symptoms, and enhancing quality of life (3).

Respiratory training is essential in PR, strengthening respiratory muscles and alleviating dyspnea (4). However, certain traditional exercises (e.g., Positive Expiratory Pressure Therapy, Threshold Inspiratory/Expiratory Muscle Training) can be monotonous and difficult to sustain over time, particularly due to their repetitive, non-interactive nature (5, 6). Harmonica playing provides a novel alternative by combining pursed-lip and diaphragmatic breathing with controlled airflow, simulating respiratory training through an engaging, interactive musical activity that reduces monotony and enhances motivation (7, 8). Beyond physiological benefits, music induces positive emotions, reduces stress, and fosters a sense of accomplishment (9). Furthermore, harmonicas are cost-effective (10), with a 24-hole tremolo model from a reputable Chinese brand priced around USD 4.30. This is much cheaper than respiratory training devices like the XEEK Kuner (USD 430) and Breath Home (USD 428). Portable and requiring no extra equipment or space (11), the harmonica further minimizes costs, making it a financially advantageous adjunct to PR.

However, the benefits of harmonica playing in improving health outcomes for COPD patients remain incompletely explored. Three preliminary studies have suggested potential improvements in respiratory muscle strength, exercise capacity, breathing control, and quality of life (12–14). Nevertheless, these studies suffer from significant methodological limitations, including lack of randomization (12), small sample sizes (from 9 to 13) (12–14), and inconsistent practice regimens (10–40 min daily) without standardized guidelines on home practice duration or frequency (12–14). The studies had inadequate follow-up periods (13) and no systematic post-intervention monitoring in others (12, 14), thereby limiting the assessment of long-term impacts. Moreover, they mainly assessed physiological outcomes, like spirometry, inspiratory and expiratory muscle strength, and breathlessness, ignoring functional measures like the six-minute walk distance (6MWD) (15) and inadequately addressing psychological and social factors such as adherence and wellbeing (12–14). These gaps underscores the need for a robust randomized controlled trial with comprehensive outcome measures to evaluate harmonica-integrated PR for COPD.

This study utilizes a rigorous randomized controlled trial (RCT) design with a large sample size, extended intervention period, standardized training protocol, and comprehensive outcomes, addressing the limitations of previous research. It aims to provide robust evidence on the physiological, functional, and psychological benefits of a harmonica-integrated, tele-supervised, home-based PR program for COPD patients. The primary outcome is lung function, with secondary outcomes including respiratory muscle strength, exercise capacity, fatigue, dyspnea, mental health, self-efficacy, quality of life, adherence, and satisfaction—addressing both physiological and psychosocial factors. Findings may inform global COPD management guidelines, positioning harmonica-integrated PR as a cost-effective, accessible, and engaging alternative, particularly in areas with limited access to traditional rehabilitation services.

## 2 Methods and analysis

### 2.1 Study aims

The primary objective of this study is to assess the effectiveness of a harmonica-integrated, tele-supervised, home-based PR program on lung function in patients with COPD, compared to a standard PR program without harmonica integration. Secondary objectives include evaluating the intervention's effects on respiratory muscle strength, exercise capacity, fatigue, dyspnea, symptom burden, mental health, self-efficacy, quality of life, social support, adherence, and satisfaction.

### 2.2 Study design

A single-center, two-arm study will be conducted at a tertiary hospital in Guangzhou, China to compare the effects of a harmonica-integrated, tele-supervised home-based PR program with those of a standard PR program on lung function and overall health in COPD patients. A total of 248 adult participants, clinically diagnosed with COPD but free of severe comorbidities, significant cognitive impairments, and prior exposure to the intervention components will be enrolled. The intervention will span 6 months, with clinical assessments performed at baseline (T0, the day the intervention begins), and 1 month (T1), 3 months (T2), and 6 months (T3) post-baseline. Figure 1 illustrates the participant flow through the study. This study registered at ClinicalTrials.gov (NCT05995847).

**Figure 1 F1:**
[figure not shown]
Flowchart of the randomized controlled trial protocol. FEV_1_%, Forced expiratory volume in one second of predicted; PImax, maximum inspiratory pressure; PEmax, maximum expiratory pressure; 6MWT, Six-Minute Walking Test; CIS-Fatigue, Checklist Individual Strength-Fatigue; FACIT-F, Functional Assessment of Chronic Illness Therapy-Fatigue; mMRC, modified Medical Research Council; CAT, Chronic Obstructive Pulmonary Disease Assessment Test; CCQ, Clinical Chronice Obstructive Pulmonary Disease Questionnaire; HADS, Hospital Anxiety and Depression Scale; CSES, Chronic Obstructive Pulmonary Disease Self-Efficacy Scal; SGRQ, St. George's Respiratory Questionnaire; MSPSS, Multidimensional Scale of Perceived Social Support; T0, baseline; T1, 1 month post-baseline; T2, 3 months post-baseline; T3, 6 months post-baseline.

### 2.3 Eligibility and sample size

Eligible patients must have a clinical diagnosis of COPD and a post-bronchodilator forced expiratory volume in one second (FEV_1_) to forced vital capacity (FVC) ratio of < 70%. Exclusion criteria include recent COPD exacerbations (within 6 weeks), resting oxygen saturation (SpO_2_) below 88% on room air or inadequate oxygenation despite supplementation; as well as severe dyspnea with Modified Medical Research Council (mMRC) grade 4, recent myocardial infarction, unstable angina, severe arrhythmias (e.g., ventricular arrhythmias or rapid atrial fibrillation), or pulmonary hypertension with right heart failure. Additional exclusions include comorbidities affecting physical activity (e.g., neurological disorders, cancer, significant musculoskeletal issues), cognitive impairments, and inability to communicate in Chinese. Furthermore, those with prior participation in PR within 6 months, or regular experience playing harmonica or similar wind instruments, are excluded to ensure baseline equivalence, minimize learning and behavioral biases, and avoid psychological effects, thereby enhancing the validity and reliability of the study outcomes.

Based on an anticipated minimum clinically important difference (MCID) of a 4% increase in percent predicted FEV_1_ (FEV_1_%) and a standard deviation of 10% (16), each group will require 99 participants to achieve 80% power at a 0.05 two-tailed significance level. Considering a 20% dropout rate, the study plans to enroll 248 patients (124 per group) (17).

### 2.4 Recruitment

Participants will be recruited using a comprehensive, multifaceted approach to ensure a broad and inclusive reach. Recruitment efforts will include advertisements in the hospital's outpatient clinics, referrals from healthcare providers, and telephone outreach to former outpatient and inpatient COPD patients. In addition, we will employ online recruitment strategies, such as WeChat and community outreach. The research team will meticulously screen interested individuals based on stringent inclusion and exclusion criteria to determine their eligibility. Enrollment will occur on a rolling basis, allowing eligible candidates to join the study as they meet the criteria and space is available. All eligible candidates will receive detailed information about the study through an information letter and an informative flier. Those who agree to participate will provide written informed consent as part of the enrollment process.

### 2.5 Randomization

Participants will be randomly assigned in a 1:1 ratio to either the intervention or control group using a computer-generated randomization sequence developed by an independent statistician unaffiliated with the recruitment process. To ensure allocation concealment, the sequence will be sealed in opaque, sequentially numbered envelopes. Upon enrollment, the recruitment coordinator, who does not have prior access to the allocation sequence, will open the corresponding sealed envelope to assign each participant to their respective group. The recruitment coordinator will then inform participants of their group allocation and provide the necessary materials, including disease education manuals, rehabilitation training diaries, elastic bands, and portable pulse oximeters for monitoring oxygen saturation during exercises. Participants allocated to the harmonica-integrated group will additionally receive a harmonica. Additionally, the recruitment coordinator will communicate the time and location of each session to the participants.

### 2.6 Blinding

This study employs a partially blinded design to minimize potential biases. Care providers responsible for delivering the interventions—including rehabilitation instructors, harmonica instructors, home-training supervisors, and home-training recorders—are blinded to group allocations and the overall study protocol. They are informed only of the specific treatments they are to administer without knowledge of the study protocol and participants' group assignments. Outcome assessors conducting evaluations are blinded to the group allocations to ensure objective assessment of study outcomes. The data analyst performing the final data analysis is also blinded to group assignments to maintain objectivity in data interpretation. Although the recruitment coordinators are aware of group assignments for administrative purposes, they do not engage in any intervention, assessment, or follow-up tasks to minimize potential biases. Due to the nature of the intervention, patients cannot be blinded. However, potential biases will be minimized by standardizing intervention protocols and using objective outcomes as primary measures.

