#### 2.7.3 Harmonica sessions

Participants in the intervention group will receive three progressive harmonica lessons (T0, T2, T3), conducted by professional music instructors, designed to optimize skill development. The initial lesson (T0) will cover harmonica fundamentals, including instrument anatomy, maintenance and cleaning, harmonica-based breathing techniques, and basic performance skills, establishing a foundation for subsequent lessons. At baseline, simple songs will be selected to build patients' confidence. Participants will be provided with structured written materials outlining practice methods and musical exercises. Subsequent lessons (T2 and T3) will introduce classical songs of increasing difficulty, building on foundational skills and progressively enhancing technical proficiency and enjoyment. Throughout the six-month intervention, participants will engage in a daily 30-min continuous (no-break) practice of a specified set of songs.

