#### 2.7.4 Tele-supervision and guidance for intervention group

Upon randomization, a WeChat group will be established for each intervention cohort, including participants themselves, their family members (if they choose), a home-training supervisor and recorder, a rehabilitation instructor, and a harmonica instructor. For participants with limited device familiarity or access, one-on-one personalized WeChat training will be conducted at baseline, including video tutorials, content uploads, and interaction with PR staff. Family members will be trained if needed to assist with remote monitoring.

Participants will upload daily videos of their training and harmonica playing, report training duration, and complete rehabilitation training diaries documenting exercise and harmonica practice times. The supervisor and recorder will independently review the videos to verify adherence, and discrepancies will be resolved through double-checking the video recordings. Additionally, the supervisor and recorder will send daily reminders, track attendance, and note any absences. Rehabilitation and harmonica instructors will conduct real-time video assessments of participants' techniques, providing immediate feedback, personalized guidance, and addressing participant queries.

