## 3 Discussion

By leveraging the respiratory benefits of harmonica playing—which simulates respiratory training and incorporates the advantages of music therapy—along with the convenience of home-based training and the instant support of tele-supervision, this study aims to evaluate the effectiveness of a harmonica-integrated, tele-supervised home-based PR program. This innovative approach may offer an accessible, affordable, and enjoyable non-pharmacological treatment option for patients with COPD.

With a robust sample size of 248 participants, a six-month intervention, standardized protocols, and comprehensive outcome measures, the study enhances statistical power, generalizability, and long-term assessment (41, 42). Key design features include a partially blinded methodology, where care providers, outcome assessors, and data analysts are unaware of group assignments, minimizing bias and ensuring objective evaluation (43). The home-based approach improves accessibility for remote or mobility-limited patients, reduces travel and costs, and may lower infection risks compared to clinic settings (44, 45). Tele-supervision involves roles such as home-training recorder, supervisor, and instructors, providing real-time guidance and technique correction. Communication via WeChat fosters a supportive community, while video recordings ensure objective adherence data (46). Harmonica training progresses from basic music theory and breathing techniques to advanced playing skills, promoting mastery and enjoyment. Concurrently, comprehensive PR sessions include breathing exercises (e.g., pursed-lip, diaphragmatic) and physical activities (e.g., air cycling, hip bridge, resistance band stretching) to enhance respiratory and overall muscle function (41, 47). Regular technical assessments and introductory guidance support effective home-based training.

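### The protocol claims that care providers are blinded to allocation, but in the intervention arm they teach, watch or share a chat group with the harmonica component that defines the arm

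*Protocol article*

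**What the plan says.** Section 2.6 (Blinding) calls the design partially blinded and lists who is blinded. For care providers it names four roles, "including rehabilitation instructors, harmonica instructors, home-training supervisors, and home-training recorders—are blinded to group allocations and the overall study protocol". It then explains how this is meant to work: "They are informed only of the specific treatments they are to administer without knowledge of the study protocol and participants' group assignments". Outcome assessors and the data analyst are listed separately as blinded. Participants are acknowledged to be unblinded, and recruitment coordinators know the assignments.

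The Discussion (Section 3) presents this as a key design feature, "where care providers, outcome assessors, and data analysts are unaware of group assignments, minimizing bias and ensuring objective evaluation".

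The sections on delivery describe what these staff do. On equipment, Section 2.5 says: "Participants allocated to the harmonica-integrated group will additionally receive a harmonica". On teaching, Section 2.7.3 says: "Participants in the intervention group will receive three progressive harmonica lessons (T0, T2, T3), conducted by professional music instructors". Section 2.7.4 sets up a WeChat group for the intervention cohort whose staff members are "a home-training supervisor and recorder, a rehabilitation instructor, and a harmonica instructor". It also says: "Participants will upload daily videos of their training and harmonica playing", and "The supervisor and recorder will independently review the videos to verify adherence". Section 2.8 gives the control arm the same programme without harmonica sessions. Section 2.8.1 gives it a separate WeChat group, for which a supervisor, a recorder and a rehabilitation instructor are listed but no harmonica instructor.

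**The concern.** The harmonica component is the planned difference between the arms. Someone who teaches it, or watches a participant play it every day, knows which treatment that participant is receiving. Section 2.6 nevertheless says that these people do not know the group assignment, and the Discussion takes credit for it.

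Two things are at stake. First, these staff send daily reminders, give feedback and correct technique over six months. If they know the treatment, encouragement could differ between arms, and a reader told that providers were blinded would discount that possibility. Second, the supervisor and recorder verify adherence. Adherence is a secondary outcome (Table 2 and Section 2.9.2.11), and the per-protocol sensitivity analysis in Section 2.10 is limited to participants who adhered fully. For this outcome the care staff act as the assessors, so the blinding of the separate outcome assessors does not cover it.

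If the statement stands, it will pass into the trial report and into any later assessment of risk of bias.

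**Working it through.** The check is a comparison of texts. The only figure used is the planned 124 per group, which follows from the plan's own inputs in Section 2.3 (difference 4, SD 10, two-sided alpha 0.05, power 80%, dropout 20%):

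- n per group = 2 × (1.960 + 0.842)² × 10² / 4² = 98.1, rounded up to 99, as stated.
- 99 / (1 − 0.20) = 123.75, rounded up to 124 per group, or 248 in total, as stated.

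The sample size reproduces and does not depend on who is blinded.

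**Each role in the intervention arm, set against Section 2.6**

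| Role said to be blinded | What the delivery sections have the role do | Can the role be unaware of the treatment? |
|---|---|---|
| Harmonica instructor | Teaches harmonica lessons, which only the intervention arm has (2.7.3, 2.8) | No |
| Home-training supervisor | Belongs to the intervention WeChat group and reviews videos that include harmonica playing (2.7.4) | No |
| Home-training recorder | As for the supervisor (2.7.4) | No |
| Rehabilitation instructor | Belongs to the same group as the harmonica instructor and assesses technique by video (2.7.4) | No, on the natural reading that the uploads go to that group; the harmonica instructor's membership already points to the treatment |

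All four roles are exposed, for all 124 planned intervention participants.

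**Does it matter whether staff work in one arm or both?** The article does not say which, so take each case.

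- Staff serve both arms: they see one chat group with harmonica and one without, and know who is in each.
- Staff serve one arm only: those in the intervention arm still know that their participants play the harmonica. They might not know that a comparison group exists, but they know the treatment given.

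In both cases intervention-arm staff know the treatment.

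**Control arm.** The absence of harmonica content reveals allocation only to someone who knows that the other arm has it. Section 2.6 says staff are not told the protocol, and no section says that staff work across arms. The question is open for control-arm staff.

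**Which outcomes are reached?** Section 2.6 assigns evaluations to separate blinded assessors, and no section has care providers measuring FEV1%. The routes left are how participants are encouraged and coached, and how adherence is recorded.

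**The case against.** The strongest defence is that Section 2.6 explains what it means: staff are told only about the treatment they give. Staff who do not know the hypothesis, or that a second arm exists, have less reason to favour one treatment. That may be achievable, and it would be worth having. It stands as a reason not to say that the protection is worthless. It does not rescue the wording, because Section 2.6 asserts blinding to allocation as well as to the overall protocol, and the Discussion repeats only the allocation part.

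A second defence is that provider blinding is infeasible when staff teach an instrument, so the design is not at fault. That is right. The fault lies in the description.

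A third is that safeguards are already in place. Section 2.8.1 applies the same recording methods and daily prompts to both arms, Section 2.6 commits to standardised intervention protocols, and Section 2.7.4 has two people review videos independently and recheck disagreements. These points stand. They reduce the room for unequal handling and make a request for scripted prompts unnecessary. They do not make the staff blinded.

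A reader might also infer more than the article supports:

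- That control-arm staff are equally unblinded. This needs knowledge of the other arm, which no section attributes to them.
- That FEV1% or the other effort-dependent tests are measured with bias. The blinded assessors are not contradicted anywhere.
- That all patient-reported outcomes lose a protection they were credited with. The limitations text in the Discussion already warns of expectation bias from unblinded participants, and its list of mitigations does not include provider blinding.

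**Conclusion.** The statement that care providers are blinded to group allocation is wrong as written for the intervention arm, in both Section 2.6 and the Discussion. It covers four roles and 124 planned participants. For the control arm the article does not settle the matter.

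The consequence is limited. Direct measurement bias in the primary outcome does not follow, because assessor and analyst blinding is unchallenged. Any effect of provider awareness on FEV1% would have to act through how participants train, and the article gives no basis for estimating its size. Adherence is more directly exposed, because staff who know the treatment determine it and the per-protocol set depends on it.

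The conclusion assumes that the delivery sections describe what will happen, and that the uploaded videos are seen by the staff named for each chat group. The correction should be made before results are reported, since it changes what protection the report may claim. It does not threaten the primary analysis and alters no figure.

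**What to change.** 1. In Section 2.6, state that participants are unblinded and that care providers know the treatment they deliver. If it is true, add that they are kept unaware of the hypothesis and the overall protocol. Confine the blinding claim to outcome assessors and the data analyst.
2. In the Discussion, take care providers out of the sentence on who is unaware of assignment, and add provider awareness to the limitations next to the lack of participant blinding.
3. In Sections 2.9.2.11 and 2.10, state that adherence, and the per-protocol set derived from it, is determined by staff who are not blinded to treatment.
4. Optionally, report the number of staff contacts per participant by arm, taken from the WeChat records, so that a reader can see whether attention differed.

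Items 1 to 3 cost a few sentences and a less favourable description of the blinding. Item 4 costs a count from records that the WeChat groups should already hold. No arm, assessment, sample size or primary analysis changes.
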